**Table 1. National Adherence Guidelines minimum package of interventions**

| **Approach** | **Intervention** |
| --- | --- |
| Education and counselling | 1. Fast track initiation counseling* 2. Enhanced adherence counseling for unstable patients* 3. Child disclosure counseling for children living with HIV |
| Repeat prescription collection strategies | 1. Adherence clubs* 2. Spaced and fast lane appointment systems 3. Decentralised medication delivery* |
| Patient tracing | 1. Early tracing of all missed appointments* |
| Integrated HIV, TB, NCD care | 1. Integrated consultation and counselling |

*Indicates interventions included in this evaluation

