## **e. Early Tracing of Patients Lost to Follow Up**

Early tracing of patients who miss an appointment by 5 days or more seeks to identify patients who have not returned to the clinic for scheduled appointments and attempts to return them to care. This intervention requires obtaining permission from patients to contact them and maintaining up to date contact information in patient records. The goal is to reduce clinic loss to follow up and improve patient outcomes by identifying those who have missed appointments and seeking to encourage them to return to care.

| *Primary outcome:* | Proportion of patients who miss a scheduled appointment by 5 days or more who return to care within 3 months of tracing |
| --- | --- |
| *Eligibility:* | All adult patients who fail to return for a scheduled appointment within 5 to 90 days from their appointment date |
| *Sample size:* | 576 (288 per arm; 24 per cluster) |
| *Data sources:* | Tier.Net; tracing registers or logbooks; appointment books; consent forms; other registers or records that document tracing attempts and interactions with patients |

In the early implementation phase at the study clinics, the government will also test fast track/spaced appointments for patients on antiretroviral therapy. This strategy is targeted at patients who are stable on treatment as defined above and therefore does overlap with the adherence club and decentralized medication delivery populations. If fast track/spaced appointments are implemented for the same patients enrolled in the adherence clubs or receiving decentralized medication delivery in the pilot facilities, the interventions evaluated will then be “adherence clubs plus fast tracked/spaced appointments” and “decentralized medication delivery plus fast tracked/spaced appointments,” as it will not be possible to distinguish between the impacts of the two interventions.

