## **e. Data Analysis Objective 7**

For Objective 7, we will estimate the incremental cost to the provider (NDOH) of delivering each intervention per patient receiving the intervention, per patient achieving the primary outcome, and per clinic population eligible for the intervention. We will start with bottom-up costing of the resources utilized per patient served in the intervention clinics and recorded in the data sets collected under Objectives 1-5. Costs to be included are those identified in the cost analysis of the Adherence Guidelines we previously prepared for the NDOH[16]. These will be categorized as incremental or non-incremental to indicate whether they are additional budgetary expenses incurred by NDOH or a reallocation of existing resources. The quantity of each resource used by each enrolled patient will be estimated and then multiplied by the unit cost for that resource. Unit costs will be calculated from clinic invoices, NDOH and NHLS price lists, government salary scales, and other sources of actual costs incurred. We will use a top-down approach to estimate shared costs (e.g. clinic management) where necessary. We will closely follow the methods of the previously prepared cost analysis[16] to provide consistency of estimates. This analysis, in turn, follows the methods used in a number of papers we have published on the costs of HIV care in South Africa[17–19].

Once an average cost per patient receiving the intervention has been estimated, we will then estimate a cost per patient achieving the primary outcome (total cost of the intervention per site/total patients receiving the intervention), which is a preliminary measure of the cost-effectiveness of the interventions and can be compared to information from other published sources. We will also estimate the cost to offer the intervention to the full population in need at that site. The sum of these costs for all five interventions will indicate the cost to NDOH of implementing the minimum package at clinics of various sites. Finally, we will use the results of the evaluation to refine the previously completed cost analysis mentioned above[16], which will assist the NDOH to use the results for budgeting purposes.

If data collected on the TBHD cohort are sufficient to capture all resources utilized by the clinics for TB, hypertension, and diabetes care, we will use the same bottom-up cost methods to estimate the costs of care for these conditions per patient treated.

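### Objective 7 labels the summed cost of the five evaluated interventions as the cost of the minimum package, although Table 1 lists eight interventions and the sum may count stable patients twice

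*Protocol*

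**What the plan says.** Section 10e (Data Analysis Objective 7) builds the costing in steps. It estimates an average cost per patient for each intervention, then the cost of offering that intervention to everyone at the site who needs it, and then adds the results: "The sum of these costs for all five interventions will indicate the cost to NDOH of implementing the minimum package". The next sentence says that the evaluation results will be used to refine an earlier cost analysis (reference 16), which is meant to help the department with budgeting.

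Table 1 (section 3a) sets out the minimum package under four approaches, with an asterisk on each evaluated intervention:

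- The first approach, counselling, has three entries: "1. Fast track initiation counseling* 2. Enhanced adherence counseling for unstable patients* 3. Child disclosure counseling for children living with HIV".
- The second, on repeat prescriptions, also has three: "1. Adherence clubs* 2. Spaced and fast lane appointment systems 3. Decentralised medication delivery", the last also asterisked.
- The third, tracing, has one: "1. Early tracing of all missed appointments", asterisked.
- The fourth, integrated care, has one: "1. Integrated consultation and counselling", not asterisked.

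The aims in section 3c describe the evaluated interventions as a subset of the package. Section 6, which introduces Objective 7, says the five are implemented as part of it. Section 4e adds that, during early implementation, "the government will also test fast track/spaced appointments for patients on antiretroviral therapy". If the same patients also get clubs or decentralized delivery, the evaluated intervention becomes the combination.

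**The concern.** A cost for part of the package is given the name of the whole. Section 10e conflicts on this with Table 1, section 3c and section 6. Cost is a numbered objective, and sections 3b and 10g say the results are meant to inform resourcing of the national rollout. A reader who takes the reported figure at its label would believe it covers interventions such as "Child disclosure counseling for children living with HIV", for which no cost is planned.

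The sum has a second fault. It adds a term covering everyone in need for each intervention, although the protocol itself says that some of these interventions replace one another in the same patients. The figure can therefore be too narrow in the components it covers and too wide in the patients it counts. Neither fault is signalled where the sum is defined.

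**Working it through.** No stated figure needs reproducing, since the protocol gives no unit costs. The check is a count, followed by a comparison of what the sum contains with what a package cost would contain.

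**Step 1. Count the components (Table 1).** Listed: 3 + 3 + 1 + 1 = 8. Asterisked: 2 + 2 + 1 + 0 = 5. Without their own cost term: 8 − 5 = 3, namely child disclosure counselling, spaced and fast lane appointments, and integrated consultation and counselling. Section 3b confirms the running count by referring to clubs, spaced appointments and delivery as interventions 4 to 6.

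**Step 2. See whether another part of the plan costs the three.** Section 10e costs resources recorded in the data collected under Objectives 1 to 5.

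- Child disclosure counselling: section 8b limits every cohort to patients aged 18 or over, so it cannot appear in those data. It is omitted.
- Integrated consultation and counselling: no cost term, and no entry in Table 2 (data required). It is omitted.
- "Spaced and fast lane appointment systems": no separate term. Section 4e allows these to be bundled with clubs or delivery. Section 10e costs the resources used per patient served, so bundled resources may be picked up, but nothing instructs that they should be. They are omitted unless bundled.

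Two omissions are therefore certain and one is conditional.

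**Step 3. See whether the five terms can be added.** Section 3b says interventions 4 to 6 are substitutes. Section 4 says a stable patient may receive clubs or delivery but not both. Section 8b gives Cohorts 2 and 3 the same inclusion criteria. Let N be the number of stable patients at a site; cA, cD and cS the costs per patient of clubs, delivery and spaced appointments; and pA, pD and pS the shares of N receiving each, with pA + pD + pS ≤ 1.

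- Stable-patient part of the sum, read literally: N·cA + N·cD.
- Stable-patient part of a package cost: N·(pA·cA + pD·cD + pS·cS).
- Difference (sum minus package cost): N·[(1 − pA)·cA + (1 − pD)·cD − pS·cS].

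As an illustration under stated assumptions, let cA = cD = c, pA + pD = 1 and pS = 0. The sum gives 2Nc where Nc is needed, so this part is doubled.

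**Step 4. Combine.** Let K be the cost of child disclosure counselling and integrated consultation together. Then

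sum minus package cost = N·[(1 − pA)·cA + (1 − pD)·cD − pS·cS] − K.

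With costs that are not negative, the first two terms push the sum up, while pS·cS and K push it down. The documents give none of cA, cD, cS, K or the shares, so neither sign nor size can be determined.

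**Step 5. Test the obvious repair.** Adding spaced appointments as another term for all stable patients would give N·(cA + cD + cS), a third count of the same people. Adding the missing lines is not enough unless the stable population is also divided.

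**The case against.** The strongest reply is that this is one loosely worded sentence. The asterisks in Table 1 and the wording of sections 1, 3c and 6 show which five interventions are evaluated, so an attentive reader would know what was costed. The objective is descriptive, and no randomised comparison depends on it. All of that stands and keeps the point modest. It does not remove the contradiction: section 10e defines a reported quantity, and anyone following it would publish a figure with the wrong scope.

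Several stronger readings are tempting, but the documents do not support them.

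- *The national budget will be understated.* Section 10e takes budgeting through a refined version of reference 16, not directly through the five-item sum. Its contents are not shown, and it may already cost the other components. The possible double count also pushes the other way.
- *All three unevaluated interventions are certainly left out.* That is certain for two. Spaced appointments may be absorbed into club or delivery costs under section 4e.
- *The package will look cheaper per outcome than it is.* Section 10e plans cost per outcome intervention by intervention, and no ratio using the five-item sum is stated. Table 3 also has a cost per 1000 patients, which is correctly tied to the mix of interventions actually observed.
- *Three of eight indicates the share of cost missing.* It is a count of components, and any percentage of cost would be a guess.

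One defence of the sum is that the population needing each intervention could be read as only those assigned to it, in which case there is no double count. Section 10e does not say so, and the shared eligibility of Cohorts 2 and 3 points to the literal reading. The double count is therefore possible rather than established.

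**Conclusion.** The point holds as a mislabelled and mis-scoped cost figure. Five of the eight components have a cost term. Two of the other three are certainly outside the sum, and the third is outside unless bundled. Read literally, the sum also counts stable patients under both clubs and delivery. It is therefore not the cost of the minimum package, and whether it is too high or too low cannot be settled from the protocol.

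This rests on Table 1 being the definition of the package and on the literal reading of the population each cost term covers. The label is wrong on the first ground alone. The correction is worth making because the figure belongs to a numbered objective and is addressed to policymakers, but the effectiveness results under Objectives 1 to 5 do not depend on it.

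**What to change.** Amend section 10e as follows.

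1. Call the sum the cost of the five evaluated interventions.
2. Divide the stable population at each site among the substitute strategies (clubs, delivery and, where used alone, spaced appointments), and state the shares used, instead of adding a term for all stable patients under each.
3. Where section 4e treats spaced appointments as part of the club or delivery intervention, include their resources in that intervention's cost, so that cost and effect refer to the same thing.
4. Report a minimum-package total only if the remaining components are added as separate lines with a stated source. Reference 16 could serve if it contains them. Otherwise report no package total.

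This needs no new patients and no change to design or data collection in the cohorts. The price is a narrower label, a short rule for allocating stable patients, and a little extra costing work if a whole-package figure is wanted.

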## **f. Data Analysis Objective 8**

For Objective 8, we will describe retention in each stage of TB, hypertension, or diabetes care over time using simple proportions for each stage in the care cascade, stratified as data allow by clinic, province, sex, age group, and HIV status. Estimates will be presented alongside their corresponding 95% confidence intervals to allow evaluation of whether adequate precision was achieved. We will describe time to events (primary outcome, loss to care) using Kaplan-Meier curves. Finally we will look for predictors of poor retention for each condition using logistic regression and Cox proportional hazards regression.

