| Overall impact (Objective 6) | Proportion of population in need at each clinic who achieve the short term primary outcomes defined above. | Proportion of population in need at each clinic who achieve the long term primary outcomes defined above. |
| Cost  (Objective 7) | Average cost per patient receiving an adherence intervention | Average cost per primary outcome achieved; average cost per 1000 patients receiving the observed mix of interventions |
| TB, hypertension, and diabetes (Objective 8) | For each condition, proportion of patients eligible for treatment who have 80% visit compliance in the first three months after diagnosis (S) and who achieve disease control at the six-month visit after diagnosis (L) as indicated in “Primary Care 101,” the NDOH’s guide for primary health clinic services[15]. The six-month visit will be represented by the visit closest to six months within the window of 5-8 months after diagnosis. The disease control indicators to be measured, with page references for Primary Care 101, are:  TB: cured or treatment completed indicated as the patient’s status at 6 months (page 57)  Hypertension: blood pressure controlled at 6-month visit, with control defined as < 140/90 (or 120/70–140/80 if diabetes, or <130/80 if CVD, heart failure or kidney disease) (page 74)  Diabetes: random glucose < 8 or HbA1c ≤ 7% at 6 month visit (page 71) | Among patients screened, prevalence of pre-diabetes elevated blood sugar (defined by Primary Care 101 as random glucose between 7.8 and 11) and pre-hypertension elevated blood pressure that require monitoring  Proportion of patients diagnosed with pre-diabetes or pre-hypertension who a) progress to diabetes and hypertension; or b) remain in care and receive appropriate monitoring for their condition over 12 months  Prevalence of diabetes, hypertension and TB among patients screened  Proportion of diagnosed patients initiated on appropriate treatment  Proportion of patients on treatment retained in care at 12 months. Loss to follow up will be defined as being 30 days late for a scheduled appointment.  Demographic and clinical characteristics of patients who do and do not achieve primary outcomes. |

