For all outcomes under Objectives 1-5 and 8, retention in care will be defined as (1-% attrition), with attrition calculated as the sum of reported deaths, loss to follow up, and reported transfers to other facilities. Retention will thus be interpreted as “retained in care at facility,” since the outcomes of patients who transfer will not be known. Where national identification numbers are available, the national death registry will be searched to locate unreported deaths. Loss to follow up will be defined as failure to attend the clinic within 90 days of a scheduled appointment, as stated in the Adherence Guidelines (Table 7 page 49).

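### Objective 8 plans a Kaplan-Meier curve for a primary outcome defined only as fixed-window proportions; if patients who leave are censored, the curve overstates achievement

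*Protocol*

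**What the plan says.** Section 10f makes simple proportions with 95% confidence intervals the main description of the care cascade ("using simple proportions for each stage in the care cascade"). It then adds: "We will describe time to events (primary outcome, loss to care) using Kaplan-Meier curves". It gives no censoring rule and names no method for competing events.

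Table 3 in section 10a defines the primary outcome for each condition in two parts. The short-term part is the "proportion of patients eligible for treatment who have 80% visit compliance in the first three months after diagnosis (S"). The long-term part concerns those "who achieve disease control at the six-month visit after diagnosis (L"), read at the visit closest to six months within a window of 5-8 months. Both are proportions of patients eligible for treatment.

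The text below Table 3 applies expressly to Objective 8. It defines retention as the complement of a composite: "with attrition calculated as the sum of reported deaths, loss to follow up, and reported transfers to other facilities". It adds: "Retention will thus be interpreted as “retained in care at facility,” since the outcomes of patients who transfer will not be known".

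Section 10f does not say whether loss to care means this composite or loss to follow-up alone. Loss to follow-up itself has two definitions that reach Objective 8: 30 days late in Table 3, and 90 days in the text below it.

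**The concern.** The primary outcome is a status at the end of a window or at one visit, not an event with a natural onset time. A time-to-event curve for it would largely trace when visits were scheduled.

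Leaving care matters more. A patient who dies cannot reach disease control, and one who is lost or transfers cannot be seen to reach it at that facility. Censoring such patients assumes they would have succeeded at the same rate as those who stayed. The curve then describes a population without attrition, whereas Objective 8 is meant to show where patients drop out of the cascade. Section 10g says the Department of Health will use the results to target and budget the rollout. Those readers could be shown a curve and a proportion for the same outcome that do not agree, with no explanation.

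**Working it through.** The protocol states no success, loss, death or transfer rate for Objective 8, so there is no figure of its own to reproduce. All rates below are assumptions.

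**Is there any other reason to censor?** Section 9c gives every patient at least 14 months of record review after enrolment. The three-month and 5-8 month windows therefore close for everyone, and administrative censoring plays no part. Two cases remain. If leavers stay in the risk set to the end of the window, one minus Kaplan-Meier (1-KM) equals the simple proportion and the curve adds little. If leavers are censored at exit, the curve is biased upwards.

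**Size for the primary-outcome curve.** Let F1 be the true share of eligible patients who achieve the outcome and F2 the share who leave first.

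- Constant hazards: H = -ln(1 - F1 - F2), h1 = H × F1/(F1 + F2), and 1-KM = 1 - exp(-h1).
- Outcome seen only at the six-month visit, with all attrition earlier: 1-KM = F1/(1 - F2).

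Example with F1 = 0.50 and F2 = 0.25. Under constant hazards, H = -ln(0.25) = 1.386, h1 = 1.386 × 0.50/0.75 = 0.924, and 1-KM = 1 - exp(-0.924) = 60.3%. With all attrition earlier, 0.50/0.75 = 66.7%.

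| Attrition F2 (true F1 = 50%) | 1-KM, constant hazards | Excess (points) | 1-KM, attrition before visit | Excess (points) |
|---|---|---|---|---|
| 5% | 51.6% | 1.6 | 52.6% | 2.6 |
| 10% | 53.4% | 3.4 | 55.6% | 5.6 |
| 20% | 57.7% | 7.7 | 62.5% | 12.5 |
| 25% | 60.3% | 10.3 | 66.7% | 16.7 |

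The excess grows with the true share. Over the same attrition range it runs from 1.2 to 13.3 points at a true 40%, and from 2.6 to 23.3 points at a true 70%, across the two models.

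**Loss-to-care curve, two readings.**

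- Composite of death, loss and transfer: every exit is an event and nothing competes. With 20% lost and 5% dead or transferred, 1-KM = 25.0%, which is the true composite. The bias is zero.
- Loss to follow-up only, with death and transfer censored (constant-hazards formula, F1 = lost, F2 = dead or transferred):
  - 15% and 5%: 1-KM = 15.4%, excess 0.4 points.
  - 20% and 10%: 1-KM = 21.2%, excess 1.2 points.
  - 30% and 15%: 1-KM = 32.9%, excess 2.9 points.

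**The case against.** The strongest reply is that section 10f never says leavers are censored. A censoring rule is commonly left to the statistical analysis plan, which is not at hand, and a rule that keeps leavers at risk to the end of the window would remove the bias. This stands as far as it goes: the overstatement is conditional on the usual handling. It does not rescue the curve, because with leavers kept at risk it only repeats the proportion, and a time-to-event version of the outcome is still undefined.

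A second reply is that only death strictly rules out disease control. Counting lost and transferred patients as not achieving it is a choice of target. That is true, but the protocol makes a similar choice for retention by reading it at facility level, and Table 3 takes all patients eligible for treatment as its denominator. The exclusion in section 8b of patients with a recorded intention to transfer also points towards the lower end of the attrition range.

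Three stronger readings are tempting, and the protocol does not support them.

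- *Both curves are overstated.* In the loss-to-care curve the lost patients are the events, so they cannot also be censored. Under the composite definition the bias is zero.
- *The overstatement is 9 to 27 points.* This follows if 90% of those who stay succeed and 10-30% leave first: 90% against 0.9 × 90% = 81% at one end and 0.7 × 90% = 63% at the other. Both inputs are chosen, and nothing in the protocol supports them.
- *The reported control and completion figures would fall once this is corrected.* Those figures are the Table 3 proportions, already defined on all eligible patients. They would not change.

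**Conclusion.** The point holds for the primary-outcome curve. Section 10f names a time-to-event method for an outcome that Table 3 defines only as fixed-window proportions. If patients who die or leave are censored, 1-KM exceeds the facility-level share achieving the outcome by about 2 to 17 points. That range rests on an assumed true 50%, 5-25% attrition, and the two attrition models shown.

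For loss to care, the defect is an undefined term. Kaplan-Meier is valid for the composite. For loss to follow-up alone the expected bias is small, about 0.4 to 3 points under the assumed rates.

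The consequence is limited to supplementary curves in an objective that section 10b calls descriptive. The simple proportions are not affected, provided all eligible patients stay in the denominator, and neither are the comparisons under Objectives 1-5. Priority is low.

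**What to change.** In section 10f:

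1. Remove the Kaplan-Meier curve for the primary outcome and rely on the Table 3 proportion of all patients eligible for treatment. If a curve over time is wanted, define the event time and plot an Aalen-Johansen cumulative incidence with death, loss and transfer as competing events.
2. State what loss to care means. If it is the attrition composite of section 10a, keep Kaplan-Meier and label the curve as that composite. If it is loss to follow-up alone, use cumulative incidence with death and transfer as competing events.
3. Reconcile the 30-day and 90-day definitions of loss to follow-up for Objective 8, since they date the event differently.

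The cost is the rewording of one analysis paragraph. Section 10a already treats deaths, losses and transfers as separate components, so no new data are needed, and the Table 3 results stay as they are.
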